## 1 PROJECT SUMMARY

Objectives of this prospective multicenter randomized cross-over study are to evaluate the influence of two dialysis treatments (HD vs post-dilution HDF) with four high-flux (polysulfone or polyethersulfone) dialyzers i) in the clearance evaluation for small, middle and large molecular weight substances and ii) in the modification of several biological responses including parameters of inflammation and nutrition. In addition, a comparative quantification of perdialytic albumin losses using either a partial collection of continuous spent dialysate or the total dialysate collection will be performed in a subgroup of patients. Primary outcome will be  $\beta$ 2-microglobulin removal. Secondary outcomes will be i) extraction of other uremic solutes ii) parameters of inflammation and nutrition and iii) comparative quantification of perdialytic albumin losses.

32 chronic kidney disease patients treated with extrarenal replacement therapy and issued from 4 dialysis centers will be assigned to receive either post-dilution HDF (2 first centers) or conventional high-flux HD (2 other centers) for 4 weeks. During this period, all patients will be sequentially dialyzed with 4 different dialyzers (one/week): Leoced 21HX, Polypure 22S+, Rexasys 27H and VIE-21A. The sequence of dialyzers use will be randomly assigned. All patients in a given center will follow the scheme allocated to this center.

Dialysis conditions will remain unchanged for each patient: 3 sessions/week, 3-4 hours/session, blood flow (QB) of 300-400mL/min, ultrapure bicarbonate buffered dialysate, dialysate flow (QD) in the range 500-700mL/min.

Blood samples will be drawn weekly during the midweek dialysis session before and after dialysis. Routine laboratory analyses including serum urea, creatinine and PO4 (all being evaluated pre- and post-dialysis) will be locally performed. Specific biomarkers including serum  $\beta$ 2-microglobulin, myoglobin, free light chain  $\kappa$ , Beta Trace Protein, myostatin, orosomucoid, CRP, TNF- $\alpha$ , IL-6, albumin and transthyretin will be performed on frozen samples in a central laboratory.

Results of this study should bring additional information on the performance and biocompatibility of the 4 hemodialyzers tested and help in personalizing device prescription according to dialysis treatment (HD or HDF) and patient profile.

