## 5 PATIENTS

#### 5.1 Inclusion criteria

- ❑ Adult patient with chronic kidney disease dialyzed for at least one month and treated with the modality used in the center (HD or HDF) for the study
- ❑ Regarding post-dilution HDF mode, patient treated with a minimum convective volume of 20L (cf EuDIAL guidelines)
- ❑ Patient treated with high permeability membrane, with high surface area dialyzer  $\geq 1,8 \text{ m}^2$
- ❑ Patient with vascular access allowing a blood flow rate with a minimum of 300 mL/min
- ❑ Patient covered by the social French health organism
- ❑ Patient informed of the study goals and having signed the informed consent

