## 7 METHODOLOGY

### 7.1 Study design, dialyzers and dialysis conditions

This study is a prospective multicenter randomized comparative cross-over trial.

Four different dialysis facilities (AURA Paris, Yvetot clinic, AIDER clinic and Toulouse university hospital center) will be involved in the study.

Eligible patients will be assigned to receive either post-dilution HDF (first two centers) or conventional high-flux HD (last two centers) for 4 weeks. During this period, all patients will be sequentially dialyzed with 4 different dialyzers (one/week, the two first sessions of the week; the

last session of the week being performed with the patient's own dialyzer and used as a wash out session): Leoced 21HX, Polypure 22S+, Rexsys 27H and VIE-21A.

The sequence of dialyzers use will be randomly assigned: per center, device × week allocation scheme will be generated by random permutation of a block of 4 (computer generation). All patients in a given center will follow the scheme allocated to this center. The randomization sequence will be centralized and computed by the statistician.

No run-in period before entering in the active study phase will be performed

Dialysis sessions will be conducted according to usual procedures of the center, with increased monitoring and control of the patients treated with the tested hemodialyzers.

Patients will be treated in HD or post-dilution HDF, according to the usual conditions, specific to each patient. The frequency of dialysis (3 sessions per week), the duration of dialysis (3- 4h), the blood flow of the extracorporeal blood circuit ( $\geq 300$  mL/min), the type (dialysate bicarbonate or other) and the dialysate flow (700 mL/min) will remain unchanged or will be documented in case of modification.

In case of need for adjustment, or changes in prescription of the medication, these changes will be documented. The modifications will respect recommendations.

[figure not shown]

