### 9.2 Principle of the analyzes

The included population will be described in terms of demographic and medical inclusion data.

Two populations of analysis are planned: the global population including all the patients with at least one dialyzer tested and the per-protocol population (PP) including all the subjects having tested the 4 dialyzers.

The main analyzes will be conducted on the PP population and additional sensitivity analyzes on the overall population.

The main analyzes will use a univariate generalized linear model integrating the variable tested as a dependent variable and the standard hemodialysis factor (2 levels: conventional HD or HDF), the dialyzer factor (4 levels) and the center factor (4 levels) as fixed factors. A full factorial model will be applied. Two-to-two comparisons will then be conducted by adjusting the alpha risk according to the Bonferonni method.

All analyses will be carried out with Statistical Package for Social Sciences version 18.0 (IBM Inc, USA).

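### HD-versus-HDF differences in pre-dialysis albumin, transthyretin and CRP cannot be separated from entry or center differences, so they cannot show a modification by technique

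*Protocol*

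**What the plan says.** The Project Summary (Section 1) states the aim as "to evaluate the influence of two dialysis treatments (HD vs post-dilution HDF) with four high-flux (polysulfone or polyethersulfone) dialyzers", first on clearance and second "in the modification of several biological responses including parameters of inflammation and nutrition". Section 9.2 gives one model for every outcome. Its fixed factors are technique, described as "the standard hemodialysis factor (2 levels: conventional HD or HDF"), dialyzer (4 levels) and center (4 levels), in a full factorial. No outcome is exempted.

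The design holds technique fixed:

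- Section 5.1 admits patients who have been on dialysis for at least a month and are "treated with the modality used in the center (HD or HDF) for the study". HDF patients must also meet a minimum convective volume.
- Section 7.1: "Patients will be treated in HD or post-dilution HDF, according to the usual conditions, specific to each patient".
- Section 7.1 places patients in "either post-dilution HDF (first two centers) or conventional high-flux HD (last two centers) for 4 weeks". Only the dialyzer order is random: "The sequence of dialyzers use will be randomly assigned: per center".
- Section 7.1: "No run-in period before entering in the active study phase will be performed".
- Section 7.4 schedules four weekly blood draws, all at midweek sessions in weeks 1 to 4.
- Section 8 lists albumin, transthyretin and CRP as pre-dialysis values only. TNF-alpha, IL-6 and the middle molecules are listed before and after dialysis.

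**The concern.** To show that a treatment modifies a marker, a plan needs either a before/after contrast in that treatment or comparable groups formed by randomization. For technique this plan has neither. The cross-over and the randomization concern dialyzers alone.

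That matters most for markers measured only as pre-dialysis levels. Such a level largely reflects the patient's condition and earlier treatment, so two groups of patients from different centers may differ on it before the study starts. Section 3 describes the nutritional effect of HDF as disputed: some studies report better nutritional status, others no effect or a fall in albumin and transthyretin. The Summary intends the results to guide device choice by technique and patient profile. A tested HD-HDF difference in these markers could be read as evidence in that dispute when it may only reflect who is treated where.

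**Working it through.** **1. The plan's own figure.** Section 9.1 gives 32 patients for pairwise comparisons at effect size 0.6, two-sided 5%, power 80%. For a within-patient comparison, n = ((z for alpha/2 + z for power)/0.6)². This gives 22 unadjusted (24 with the t distribution), 30 (32) with Bonferroni for 3 comparisons and 34 (38) for the 6 pairs among 4 dialyzers. An unpaired comparison would need 44 per group. So 32 fits a within-patient dialyzer comparison with some Bonferroni adjustment. It was not derived for HD versus HDF, and the present point does not depend on it.

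**2. Is there a contrast in technique within patients?** Sections 5.1 and 7.1 together say no: the technique is the same at entry and throughout.

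**3. Is there an entry value?** No. Each week the study dialyzer is used for the first two sessions and blood is drawn at the midweek session. The first pre-dialysis sample therefore follows one session on a study dialyzer. Weeks 1 to 4 values are not entry values, and no change from entry can be formed.

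**4. Can the 9.2 model isolate technique?** Each center uses one technique, so only 4 of the 2 × 4 = 8 technique-by-center cells are filled. The design matrix with intercept, technique and four center columns has 6 columns and rank 4. Without technique its rank is still 4. Technique adds nothing that center does not already carry. An HD-HDF contrast can only be two centers averaged against the other two.

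**5. What would the contrast return if technique did nothing during the study?** Assumptions: 8 patients per center (16 versus 16), total SD 1, within-patient correlation 0.8, four weekly values averaged per patient, t-test on patient means, 3,000 simulated trials.

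| Entry difference (SD) | Estimated HD-HDF difference (SD) | Significant at 5% | Dialyzer-by-technique contrast (SD) |
|---|---|---|---|
| 0 | -0.01 | 5% | 0.00 |
| 0.3 | 0.30 | 15% | 0.00 |
| 0.6 | 0.61 | 45% | 0.00 |
| 1.0 | 1.01 | 85% | 0.01 |

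The main contrast returns the entry difference. The dialyzer-by-technique contrast does not, because each patient's level cancels when two dialyzers are compared in the same patient.

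**6. Imprecision, which is a separate matter from bias.** With 16 versus 16 and one value per patient, the 95% half-width is t(0.975, 30) × SD × sqrt(2/16) = 2.042 × SD × 0.354. For assumed albumin SDs of 3, 4 and 5 g/L this is 2.2, 2.9 and 3.6 g/L. Averaging four values at correlation 0.8 multiplies it by sqrt(0.8 + 0.2/4) = 0.92, giving 2.0 to 3.3 g/L for SDs of 3 to 5.

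**The case against.** The strongest reply is that the study is about dialyzers. The title says so. Section 4 links technique to extraction and links anti-inflammatory action to each membrane. Section 4.2 lists CRP, albumin and transthyretin without an HD-HDF comparison, and Section 9.1 calls the study exploratory and sizes it for dialyzers. This stands as a limit on weight: the technique claim for these markers rests on the Summary's aim and the general model in 9.2. Both are nevertheless in the protocol, and neither makes an exception.

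A reader might go further and infer that any HD-HDF difference in these markers simply is the entry difference. The documents do not support that. Patients change to study dialyzers, and Section 3 attributes falls in albumin and transthyretin to protein leak that varies with the membrane. The new dialyzers could shift levels differently under HD and HDF. Without an entry value that share cannot be isolated, so the contrast is inseparable from the entry difference, not identical to it.

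A reader might also extend the point to inflammation as a whole. TNF-alpha, IL-6 and orosomucoid are measured before and after the session, so a change within the session can be formed, as it can for the reduction ratios; Kt/V likewise describes the session. The entry-level argument does not reach these outcomes, although their HD-HDF comparison remains tied to center. CRP needs a note: Section 7.4 lists it among the after-dialysis tubes, while Section 8 records it pre-dialysis only. The point concerns the pre-dialysis value.

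Finally, because 9.2 also fits center, one can say that the model would not deliver a separate technique effect at all. That is correct, and it means the aim in the Summary is unsupported by a second route. The half-widths in g/L measure chance imprecision and are no estimate of bias.

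**Conclusion.** The point holds in this limited form. For pre-dialysis albumin, transthyretin and CRP, the HD-HDF main contrast cannot be separated from differences at entry or between centers, and it cannot show that technique modified these markers. This follows from the fixed technique, the absence of a pre-study sample and the nesting of technique in center, all stated in the protocol. It needs no numerical assumption.

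The size depends on the entry difference, which the documents do not give. Under the assumptions in step 5, entry differences of 0.3 to 1.0 SD would pass through in full and be declared significant in 15% to 85% of trials. The 16/16 split, the correlation of 0.8 and the albumin SDs are all assumed.

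The markers are secondary and the study is exploratory. The primary outcome, the beta-2-microglobulin reduction ratio, and the within-patient dialyzer comparisons are not affected by this entry-level argument.

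**What to change.** - **Section 9.2:** report pre-dialysis albumin, transthyretin and CRP from weeks 1 to 4 by technique descriptively, without a test of the technique main effect and without an effect claim. Do not label them entry values.
- **Section 9.2:** for the same markers, keep the within-patient dialyzer comparisons and the dialyzer-by-technique contrast. State that the latter is tied to center and to week order, since all patients in a center follow one dialyzer sequence.
- **Section 1:** for these three markers, limit aim (ii) to differences between dialyzers within each technique.

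The cost is a change of wording and the loss of one unsupported technique claim on secondary markers. No new data are needed. Adding a sample before the first study session would allow change from entry to be analyzed, but technique would still follow center, so it would not restore a causal HD-HDF claim.

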## 2 GENERAL INFORMATION

### Title

Evaluation of the biocompatibility and performance of hemodialyzers used in different dialysis modalities: conventional hemodialysis and post-dilution haemodiafiltration

### ClinicalTrials.gov Identifier

NCT03262272, First posted: 25/08/2017

### 3 RATIONALE AND BACKGROUND

With the aging population, the number of patients receiving chronic dialysis treatment keeps increasing with an average age around 75 years old.

#### Role of dialysis

Dialysis allows the elimination of toxins of variable molecular weight.

Molecules to be purified can be schematically divided according to their molecular weight into

- Water-soluble small molecules with a molecular weight below 500 Da

These small water-soluble molecules, including urea, are easily removed by all dialysis techniques by diffusion phenomenon.

- Middle molecules of molecular weight greater than 500 Da

These middle molecules have deleterious effects and must be removed, even though a complete removal is difficult to reach. Along with diffusion phenomenon, convection method has to be performed. First middle molecule described was  $\beta$ 2microglobulin, which is known to cause amyloidosis, an inflammatory disease with high concentrations of plasma  $\beta$ 2microglobulin, in dialysis patients.

European Uremic ToXin Work Group (EUToX) has studied more than 850 publications and found 90 molecules with proven accumulation and deleterious effects in chronic kidney disease patients. The range of concentration is very wide, ranging from ng/L to g/L, and with degree of toxicity not necessarily related to its concentration. [4]

#### Consequences of dialysis: the inflammatory syndrome

The chronic microinflammatory state observed in advanced CKD (including dialysis) patients has been widely described and of multifactorial origin.

Some factors are directly related to the patient: kidney disease, associated co-morbidities, oxidative stress, infections, obesity and genetic or immunological factors. Others causing the chronic inflammatory syndrome are the direct consequences of the extracorporeal circuit including dialysis quality and biocompatibility of the membranes [1,2].

In CKD patients, inflammation is partly related to the degradation of cellular proteins, secondary to the toxicity of hyper-uremia [3]. Other factors may also be involved, such as decreased renal clearance of cytokines or sodium and fluid overload [2].

#### Dialysis techniques: conventional hemodialysis or haemodiafiltration

Currently two dialysis techniques are mainly used in France: conventional hemodialysis (HD) favoring the physico-chemical principle of diffusion and hemodiafiltration (HDF) combining both diffusion and convection.

The superiority of post-dilution HDF compared to HD for the removal of middle molecules is largely documented and explained by the contribution of convective transport to the global transfer of solutes, all the more important when molecular weight is high. Increase in convective transports in HDF has been associated with decreased inflammation and oxidative stress, improving nutritional status, anemia and quality of life of patients [5,6,7,8,9].

A recent Spanish study showed a 30% reduction in all-cause mortality when patients were treated with post-dilution HDF using convective volumes greater than 23L compared to conventional HD [6].

In order to optimize the post-dilution HDF and to obtain clinical benefits, the EUDIAL group recommended convective volumes around 20-22L per session [10].

These results on mortality are not confirmed by other studies [11,12,13]. Several preliminary studies have failed to show any impact of HDF on nutritional criteria, or rather the decline of albumin (PM=66 kDa) and transthyretin (MW=55 kDa) levels with the technique. Such decreases can be attributable to variable amounts of per-dialytic protein leak depending on the membranes used, more or less permeable and therefore more or less effective in the elimination of other middle molecules (uremic or non-uremic toxins) [9].

Albumin losses can be measured in the dialysate by different sampling techniques such as "pull-push" syringe allowing to collect continuous spent sampling of dialysate or the total dialysate collection which represents the gold standard method to evaluate mass balances achieved during dialysis for a given solute [14].

#### Molecules to be removed

In order to evaluate performance of membranes, it is therefore interesting to verify the removal of middle molecules of increasing molecular weight.

- beta-2 microglobulin (11.8 kDa)

*Pre-dialytic mean levels of serum beta-2 microglobulin were correlated with mortality in another analysis of the HEMO study [15].*

- myoglobin (17 kDa), *a marker of middle molecules in haemodiafiltration*
- beta trace protein (21 kDa), an independent risk predictor of cardiovascular mortality in hemodialysis patients [19]
- $\kappa$  free light chain (23 kDa), *to be eliminated in multiple myeloma*
- myostatin (40 kDa), *also playing a role in muscle mass*
- Orosomucoid glycoprotein (44 kDa), *inflammatory protein*

In the inflammatory process observed in CKD, cytokines, other middle molecular weight proteins, also play a fundamental role [16]. In CKD patients and hemodialysis, a huge immune change promotes the establishment and maintenance of a chronic inflammatory state.

In dialysis, this inflammation appears less marked in HDF than in conventional HD. [17]

#### Cytokines in chronic inflammation of CKD patient

In dialysis patient, the use of so-called biocompatible membranes has allowed reduction in chronic inflammation by decreasing the inflammatory response and by removing inflammatory molecules, including cytokines, during the sessions.

The study of cytokine clearance during dialysis session has been studied with different dialyzers in HDF and HD. Variations in the results could be partly explained by the short half-life of cytokines and their secretion before, during and after the session.

Two of these cytokines play a fundamental role in the inflammatory process in CKD patients [13]: IL-6 and TNF- $\alpha$ .

#### *IL-6*

Interleukin-6 is a 22 to 26 kDa protein that plays a predominantly pro-inflammatory role in the immune response. It is secreted by most immune cells, especially adipocytes, lymphocytes, fibroblasts and monocytes, in response to a physiopathological stimulus (production of endotoxins, TNF- $\alpha$ , IL-1 or oxidative stress).

Levels of IL-6 increase in patients with CKD, especially after dialysis sessions (hemodialysis or peritoneal dialysis). This can be explained by several factors:

- Bio-incompatibility of dialyzers favoring the production of cytokines
- Decreased renal clearance
- Increase of monocyte production
- Water and fluid overload
- Congestive heart failure

IL-6 appears to play a role in the inflammatory mechanism of atheromatous plaque formation. It is also involved in protein catabolism, participating in the occurrence of a wasting syndrome, and the appearance of undernutrition and sarcopenia.

#### *TNF- $\alpha$*

As a pro-inflammatory cytokine of 17 kDa, TNF- $\alpha$  plays a key role in the regulation of pro and anti-inflammatory mediators.

The increase in urea in CKD patients is the main factor associated with a significant increase in TNF- $\alpha$  production. Obesity, congestive heart failure and insulin resistance are all associated factors.

#### Other markers of inflammation of CKD

##### *C Reactive Protein*

CRP is a protein that is increased during the inflammatory response, especially of infectious cause. Its plasma levels are correlated with increases in IL-6.

##### *Albumin*

Albumin, the main plasma protein, is a key nutritional parameter. The correction of hypoalbuminemia is essential during a chronic inflammatory syndrome.

##### *Blood count and anaphylatoxin counts*

Increase in leucocytes is mainly associated with an infectious, viral or bacterial state, and secondarily with some noninfectious inflammatory reactions.

During bioincompatibility reactions, the levels of anaphylatoxins are increased, attesting of the complement system activation.

Improved hemocompatibility of dialysis membranes has significantly reduced inflammatory biological responses from the blood-membrane interaction. Recent research highlights not only the materials used in the membrane but also its surface properties such as grafting of vitamin E on some polysulfone membranes [18].

Each membrane has its own performance and hemocompatibility.

Which high permeability membrane should be chosen for which patient?

The removal performance of these membranes should be determined under actual conditions of use in order to make the most judicious choice for patients.

We propose by this work to study 4 hemodialyzers that already have CE certification for this indication.

This study aims to better advise nephrologists in their choice of prescription.

